## Abstract

**Background:**

This study aims to improve medication adherence in ischemic stroke (IS) patients using a dual-driven motivation-competence intervention framework based on the theory of protective motivation (PMT) and the medication literacy model. Therefore, this study used the WeChat platform as the intervention vehicle and innovatively introduced the AI-HEALS, including the AI intelligent question and answer system and the HEALS (Health Education Accurately Linking System), aiming to achieve personalised intervention through the intelligent terminal.

**Methods:**

The study will conduct a single-blind, single-centre randomised controlled trial in Linyi City Central Hospital, Shandong Province, with IS patients over 18 years old. The intervention group will receive routine care combined with the AI-HEALS, while the control group will receive routine care alone. Primary outcomes include changes in medication adherence levels at baseline and 1, 3, and 6 months of follow-up. Secondary outcomes encompass medication behavior management, medication literacy, self-efficacy, social cognition, psychological levels, and clinical outcome indicators.

**Discussion:**

The aim of this study was to develop an intervention programme for secondary prevention medication adherence in patients with IS by combining PMT and medication literacy models and using the AI-HEALS. Although PMT has shown effectiveness in improving health behaviors in patients with chronic diseases, systematic studies of its application to stroke patients are lacking. Our intervention framework aims to stimulate motivation, develop competence, and solidify behaviors to overcome the limitations of a single theory in complex medication scenarios. The AI-HEALS addresses the challenges of traditional mHealth interventions and is expected to improve patients’ medication literacy and adherence through precise knowledge push, dynamic interaction support, and full-cycle management. The development of the AI-HEALS helps to reduce the burden on healthcare professionals, improve the distribution of healthcare resources, and have potential health economics benefits.

**Clinical trial registration:**

https://www.chictr.org.cn, ChiCTR2500101457.

## Introduction

1

Stroke is an acute cerebrovascular disease that manifests itself as a sudden neurological impairment and can be fatal in severe cases (1). It is characterised by high morbidity, high mortality, high disability, high recurrence and high economic burden. In China, the morbidity, mortality and disability rates of stroke are higher than those in many developed countries, and the mortality rate ranks first among all diseases (2). Strokes are classified into ischemic stroke (IS), haemorrhagic stroke and subarachnoid haemorrhage, of which IS is the most common, accounting for about 73.33% of all strokes (3). During an acute attack of IS, the patient often suffers from hemiparesis, hemiplegia, hemianopsia, hemianopic blindness and aphasia, and some of the patients may also suffer from headache, vomiting and impaired consciousness. The risk of IS increases significantly with age, and doubles with every 10-year increase in the age of 55 years (4). The risk of stroke increases with age, and doubles with every 10-year increase in the age of 55 years (5). The risk of IS increases significantly with age, doubling with every 10-year increase after 55 years of age (4). The prevalence of IS is expected to continue to rise over the next 20 years as the population ages (6). Studies have predicted that the global prevalence of IS may reach 89.32 per 100,000 person-years by 2030 (6), which has become a major health challenge in China and globally.

In the early stage of IS, intravenous thrombolysis (IVT) is an effective treatment to restore cerebral blood flow and improve neurological function, but it cannot prevent cerebral atherosclerosis or eliminate the risk of recurrence. Some patients still have high rates of disability and recurrence after thrombolysis due to insufficient self-management and treatment compliance (7). Therefore, the implementation of secondary prevention measures is essential to reduce the recurrence rate and improve the prognosis. Secondary prevention targets patients who have had a stroke and aims to reduce the risk of recurrence and improve prognosis (8, 9). In the United States, approximately 700,000 ischemic strokes occur each year, a quarter of which are recurrent strokes, and the risk of death in patients with recurrent strokes is twice as high as that in patients with first-time strokes (10–12). Patients who have had a stroke and TIA have a 40% probability of having another stroke within 5 years and are at high risk for recurrent stroke (13). Most risk factors (e.g., hypertension, diabetes mellitus, hyperlipidemia, etc.) are preventable and controllable, so early secondary prevention is of great significance in improving prognosis (14). Countries have adopted a series of secondary prevention measures, including vascular risk factor management (e.g., antihypertensive, hypoglycemic, and lipid-lowering treatments) (15–19), and lifestyle interventions (e.g., Mediterranean diet, regular exercise, and smoking cessation) (20–22), which are effective in reducing recurrence rates and improving the quality of life of patients.

In this study, medication adherence is defined as the patient’s active choice and commitment to consistently follow their prescribed treatment regimen, including the correct frequency, dose, and route of administration. This concept emphasizes the patient’s voluntary role and responsibility for their own well-being, distinguishing it from the more passive notion of compliance. In secondary stroke prevention, medication adherence is key to preventing recurrence, but patient adherence is generally poor and declines over time. Data from a Swedish study showed that the proportion of patients adhering to antithrombotic medication was 86.3% 1 year after discharge, decreasing to 74.2% after 2 years (23); in China, more than one-third of patients did not use secondary prevention medication for a long period of time, and 30 to 60% of patients had low rates of knowledge, treatment, and control of stroke risk factors (24). Several studies have shown that patients’ medication adherence is poor after discharge from the hospital and that poor adherence is an independent risk factor for poor prognosis (25–28). Several intervention studies have been conducted at home and abroad to improve medication adherence, such as motivational interviewing, community nursing interventions, and smartphone apps (29–31), all of which have achieved certain results. In China, cognitive education interventions, tri-partite medication reorganisation programmes, and the ‘Seven Ones’ interventions by brain-centre health managers have also been effective in improving medication adherence (32, 33). IS patients often have a combination of chronic diseases and require multiple medications (e.g., antiplatelet agents, anticoagulants, antihypertensives, etc.), which increases the difficulty of managing medication behaviors and the need for medication management. Difficulty in managing medication-taking behaviors and the risk of medication errors, leading to a further decline in adherence (34–36). Therefore, it is particularly important to increase the level of patients’ medication literacy to improve medication adherence and overall outcomes.

Protection Motivation Theory (PMT) is a psychological theory used to explain the adoption of protective behaviors by individuals (37), proposed by Rogers in 1975 (38) and refined in 1983 (39). The theory suggests that protective behaviors are determined by a combined assessment of threat and coping, comprising three components: information sources, cognitive mediators, and coping modes. In particular, threat assessment includes perceived susceptibility, perceived severity, external rewards, and internal rewards; and coping assessment includes self-efficacy, response efficacy, and response cost. Perceived susceptibility, severity, response efficacy, and self-efficacy promote health behaviors, while external rewards, internal rewards, and response costs impede health behaviors. PMT has been widely used for disease management and health behavior change, such as prevention of skin cancer, reduction of e-cigarette smoking behaviors, and improvement of oral health knowledge (40–44). In China, PMT has also been applied in the areas of AIDS prevention and treatment, sedentary behavioral interventions for patients with coronary heart disease, and has effectively improved patients’ health behaviors and self-efficacy (45, 46).

Drug literacy refers to the ability of patients to acquire, understand, communicate, calculate and process drug information, and make correct medication decisions accordingly. The concept was proposed by Raynor in 2008 and later refined by Pouliot et al. (47, 48). Drug literacy consists of four dimensions of functional, communicative, critical and computational literacy, and five sub-dimensions of accessing, understanding, evaluating, computing and communicating drug information. Drug literacy is influenced by a combination of social, personal and health system factors (49). The conceptual model of drug literacy can significantly improve patients’ medication adherence and quality of life and reduce medication errors (50, 51). Overseas studies have improved patients’ medication literacy and adherence through hieroglyphic instructions and mobile health services (52–56). In China, drug literacy theory has been applied to interventions for patients with hypertension and myocardial infarction, effectively improving patients’ drug literacy and medication adherence (57, 58). However, there are still fewer studies on drug literacy for IS patients.

Previous studies have found that interventions to enhance patient medication adherence include patient education and health literacy promotion, pharmacist-led interventions, digital health technologies, multidisciplinary teamwork and behavioral theory-driven interventions, but these measures have limitations such as short follow-up, insufficient effect on patients with low education levels and multiple medication use, potential to exacerbate health inequalities, and insufficient economic evaluation (59, 60). Therefore, there is a need to develop more optimal strategies that incorporate patient characteristics, and multimodal interventions (PMT theory + Digital technology + Multidisciplinary collaboration) deserve further exploration.

In this study, a theoretical framework for secondary prevention medication adherence in patients with IS has been constructed and practically tested by combining Protective Motivation Theory (PMT) and a conceptual model of drug literacy (Figure 1). In this context, this study will combine the Artificial Intelligence-Health Education Accurately Linking System (AI-HEALS) intervention system (61), i.e., through the WeChat platform, to construct the “Internet + Healthcare Education “model through the WeChat platform to provide efficient solutions for IS patients. The system integrates the functions of medication consultation, health knowledge education, behavioral detection, psychological support and health reminder, and is divided into the AI intelligent Q&A system and the HEALS. The AI intelligent Q&A system will be based on the information finely scrutinised by the clinicians and pharmacists, constructed with the medical professional AI intelligent body (AI Agent), and use the large language model (deep seek) to answer the patient’s questions accurately. Provide accurate and professional medication counselling; the HEALS will make use of the convenience of the Internet to make up for the lack of traditional nursing interventions, to meet patients’ needs and to improve health outcomes. The platform constructed in this study combines the capabilities of the big language model and the HEALS, as well as the professional medication knowledge base and stroke health knowledge, to provide patients with scientific and intelligent health education services, which is expected to improve patients’ medication adherence and health management ability.

**Figure 1 fig1:**
[figure not shown]
PMT integration theory diagram.

This study aims to improve the secondary prevention medication adherence of IS patients through the intervention model of PMT combined with drug literacy education. The specific objectives are as follows:

To construct a secondary prevention medication adherence intervention programme for IS patients based on the PMT and drug literacy model, and to validate its effectiveness in improving medication adherence, self-efficacy for medication administration, drug literacy and clinical indicators in IS patients.Evaluate the effectiveness of the AI-HEALS in improving the self-efficacy of health behaviors, quality of life and psychological status of IS patients, and track the reduction in the risk of relapse and readmission.

## Methods

2

### Study design

2.1

This study is a hospital-based randomised controlled trial designed to compare the effectiveness of an intervention based on the AI-HEALS’s theory of protective motivation combined with drug literacy education with a usual care control group. The study will use quantitative methods, measured by clinical reagent tests and internationally used scales to ensure the objectivity of the trial. The study period is scheduled from June to December 2025. The control group will receive standard care, including admission education, dietary and psychological care, medication and rehabilitation care, life care, health counselling, and prognostic guidance. The intervention group will receive the AI-HEALS intervention for 3 months on the same basis. Patients will undergo questionnaires and physical examination at baseline, 3 months and 6 months post-intervention to assess changes in self medication behavior management, social cognitive and psychological indices as well as clinical health indice. The flow of the study is shown in Figure 2 and Table 1.

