### Study setting and randomization

2.2

The study remained single-blind, with participants unaware of their group allocation. All outcome assessors, including the triage nurses and laboratory staff, were blinded to the group assignments to minimise measurement bias. Data were collected and analysed by an independent third-party researcher and anonymised and coded to reduce measurement bias. Physiological outcome indicators were assessed at outpatient review by blinded triage nurses and laboratory staff who were unaware of subgroup information. The study population was screened from patients admitted to the inpatient Neurology Department between June and December 2025, following the inclusion and exclusion criteria, and the study will be conducted in the Neurology Department of Linyi Central Hospital, Shandong Province, China, in the first and second wards.

Eligible participants were randomly allocated to either the intervention group or the control group in a 1:1 ratio. The randomization sequence was generated by an independent biostatistician using a computer-based random number generator in SPSS (version 27.0, IBM Corp.). To ensure balance in group sizes over time, block randomization with a fixed block size of 4 was utilized. To control for potential baseline imbalances in key prognostic factors, the randomization was stratified by baseline NIHSS score (≤5 vs. > 5).

Allocation concealment was guaranteed to prevent selection bias. The randomization assignments were stored in sequentially numbered, opaque, sealed envelopes (SNOSE). These envelopes were prepared and held by an independent research coordinator who was not involved in the recruitment or assessment of participants. After a participant’s eligibility was confirmed and baseline data were collected, the recruiter would open the next envelope in sequence to determine the participant’s group assignment.

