### Study participants

2.3

IS patients admitted to Linyi Central Hospital in Shandong Province between June and December 2025 were selected as participants for this study. Eligibility was verified through a two-step process. First, trained staff screened electronic medical records of consecutive ischemic stroke patients. Second, a board-certified neurologist confirmed eligibility through a clinical assessment. Informed consent was obtained only after this verification was complete. Upon admission, patients will complete trial enrolment and sign a study informed consent form via face-to-face, followed by initiation of the 3-month intervention. Although participants are not recruited or initiating the intervention simultaneously, they will all follow the same intervention cycle.

To minimise the risk of cross-group contamination, we implemented stringent control measures across three dimensions: physical, personnel, and procedural. Physically, we allocated distinct follow-up times and consultation rooms for each group, with intervention materials kept under lock and key. Personnel-wise, all staff underwent standardised training, were explicitly prohibited from mentioning intervention details to the control group, and were provided with standardised response scripts. Procedurally, we implemented clear role-based segregation, advised patients at enrolment to avoid cross-group communication, and ensured effective execution of all isolation protocols through regular monitoring.

The study has been approved by the Ethics Committee of Linyi Central Hospital in Shandong Province (LCH-LW-2025031) and registration of the study protocol has been completed with the China Clinical Trial Registry (registration number: ChiCTR2500101457).

Inclusion criteria:

Meet the diagnostic criteria for first-episode ischaemic stroke (62);Age 18 years and above;Be able to operate smartphones and social media applications such as WeChat;Patients or family members signing an informed consent form.

Exclusion criteria:

Patients with cerebral haemorrhage after intravenous thrombolytic therapy;Patients with indications for mechanical thrombolysis by cerebral angiography (CTA) or other imaging tests (63, 64);Patients with severe mental illness, impaired consciousness, and inability to communicate effectively;Patients with severe gastrointestinal bleeding or serious cardiac, hepatic, or renal insufficiency;Patients with cancer or haemorrhagic disease.

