### Indicators of clinical health status

5.8

To evaluate the clinical health status of patients, we collected key biochemical and physiological indicators, including blood pressure, HbA1c, FPG, and LDL-C. BP was measured by neurology nurses upon hospital admission and at discharge. The target BP for control was set at <140/90 mmHg, with an ideal range of 120–130/70–80 mmHg; for frail older adults, this target was relaxed to <150/90 mmHg. The target level for LDL-C was <3.36 mmol/L. For glycemic control, HbA1c was used to assess long-term status in diabetic patients, with a target of <7.0%. An HbA1c level of ≥6.5% was used as a diagnostic criterion for diabetes and as a threshold for subgroup analysis. FPG, measured after at least 8 h of fasting, served as an indicator of basal glucose regulation. An FPG level between 6.1–6.9 mmol/L defined impaired fasting glucose (prediabetes) and was also used as a criterion for subsequent subgroup analysis.

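### The stated study period equals the admission window, so as written it cannot hold 6-month follow-up for most patients; the visit time origin and the blood-pressure schedule also conflict

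*Protocol article*

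**What the plan says.** **Dates.** Section 2.1: "The study period is scheduled from June to December 2025". Section 2.2 uses the same months for admissions: "The study population was screened from patients admitted to the inpatient Neurology Department between June and December 2025". Section 2.3 repeats them: "IS patients admitted to Linyi Central Hospital in Shandong Province between June and December 2025 were selected as participants for this study". It adds: "Although participants are not recruited or initiating the intervention simultaneously, they will all follow the same intervention cycle". No section gives a later date for the last visit or the end of the study.

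**Visits.** Section 2.1 places assessments "at baseline, 3 months and 6 months post-intervention". Tables 1 and 2 use 0 M, 3 M and 6 M; Table 1 puts 3 M under intervention and 6 M under follow-up. Section 3 puts the primary outcome at 3 and 6 months of follow-up. The abstract lists 1, 3 and 6 months. Section 2.3 starts a 3-month intervention at enrolment on admission, while section 2.5 runs its remote phase for about 3 months after discharge.

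**Blood pressure.** Section 5.8: "BP was measured by neurology nurses upon hospital admission and at discharge". Table 2 ticks blood pressure at 0, 3 and 6 months. Section 2.2: "Physiological outcome indicators were assessed at outpatient review by blinded triage nurses and laboratory staff".

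**The concern.** A patient admitted in the second half of the window cannot be followed for 6 months inside the same window. If the dates were kept, most 6-month values of the primary outcome would not exist, and the multiple imputation in section 5.10 would have to supply them.

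The time origin decides what the primary outcome measures. A visit counted from admission falls while the daily reminders are still running. One counted from discharge falls as they stop, and one counted from the end of the intervention falls well after they have stopped.

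For blood pressure, a secondary outcome, both the times and the assessors differ between sections. A site following section 5.8 and a site nurse following Table 2 would collect different data.

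**Working it through.** **1. Calendar.** Inputs: study period and admission window June to December 2025 (sections 2.1, 2.2, 2.3); visits at 3 and 6 months (section 3, Table 2); 80 patients and 20% attrition (section 2.4). The plan gives no completion figure to reproduce. Its attrition step does reproduce: 32 / (1 − 0.20) = 40 per group.

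Taking the widest window, 1 June to 31 December: 30 + 31 + 31 + 30 + 31 + 30 + 31 = 214 days.

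- A 6-month visit by 31 December needs entry by about 30 June: 30 days.
- A 3-month visit by 31 December needs entry by about 30 September: 30 + 31 + 31 + 30 = 122 days.

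The documents give no accrual pattern. Assuming uniform admissions:

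- 6 months: 30/214 = 14.0%, or 0.140 × 80 ≈ 11 patients.
- 3 months: 122/214 = 57.0%, or 0.570 × 80 ≈ 46 patients.

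If the months run from discharge after a stay of L days, the share is (214 − 30.4375 × m − L) / 214 for a visit at m months. The documents give no length of stay, so L is varied over an assumed 0 to 14 days:

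| L (days) | reach 3 months | reach 6 months |
|---|---|---|
| 0 | 57.3% (45.9 of 80) | 14.7% (11.7 of 80) |
| 7 | 54.1% (43.2 of 80) | 11.4% (9.1 of 80) |
| 14 | 50.8% (40.6 of 80) | 8.1% (6.5 of 80) |

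These figures fall as accrual shifts later and rise as it shifts earlier. To keep the 6-month loss within 20%, 0.80 × 80 = 64 patients would have to enter by about 30 June, in the first 30 of 214 days. For the 3-month visit, 64 would have to enter by about 30 September.

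In the other direction, a patient admitted on 31 December 2025 has the 3-month visit at about the end of March 2026 and the 6-month visit at about the end of June 2026. From June 2025 that is about 13 months, not 7.

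**2. Time origin.**

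| Place | Origin or times |
|---|---|
| Section 2.1 | 3 and 6 months post-intervention |
| Tables 1 and 2 | months from 0 M |
| Section 3 | 3 and 6 months of follow-up |
| Section 2.3 | 3-month intervention from enrolment on admission |
| Section 2.5 | remote phase about 3 months from discharge |
| Abstract | 1, 3 and 6 months |

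A 3-month visit counted from 0 M precedes the end of the remote phase by the length of stay. The 1-month assessment is in neither table and not in section 3.

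**3. Blood pressure.** Section 5.8 has admission and discharge, read by neurology nurses. Table 2 has 0, 3 and 6 months, and section 2.2 has outpatient review by blinded triage nurses. Section 2.5 says that neurological nurses deliver the intervention, and section 7 concedes that staff knew the allocations. The second in-hospital session comes 24–48 h before discharge, so a discharge reading follows it and may be unblinded. An admission reading used as baseline is protected, because section 2.2 collects baseline data before the envelope is opened.

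**The case against.** **The period may mean enrolment.** No section says that visits stop or that data are locked on 31 December 2025, and every schedule commits to 6-month data. The sponsor may well intend follow-up into 2026. That is plausible, but the text does not say it. The article's own usage points the other way: the study-period heading in Table 1 spans recruitment to 6 M, and section 2.4 places the primary comparison at the end of the study period. So a reader should not infer that the trial will fail to collect its outcomes, only that the stated dates do not permit it.

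**The loss would be administrative.** It would depend on entry date, and 1:1 blocks of 4 should keep it nearly balanced between the arms. This stands: the harm would be mainly to precision and to reliance on imputation, rather than bias between arms.

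**Stronger readings that the documents do not support.**

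- A reader might infer from section 5.8 that blood pressure is never measured at follow-up. That section does not say that these are the only readings, and Tables 1 and 2 schedule clinical indicators at 3 and 6 months.
- A reader might infer that unblinded staff certainly read blood pressure. No section says that the same nurses do both, and section 2.2 declares all outcome assessors blinded.
- A reader might take section 2.1 to mean visits 3 and 6 months after a 3-month intervention, so the last is about 9 months from entry and nobody reaches it in the window. Table 1, to which section 2.1 refers, places 3 M within the intervention, which makes this reading weak.

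**Conclusion.** The point holds as a set of contradictions in dates, time origin and blood-pressure measurement. It does not show that the outcomes are undeliverable. That the stated period is too short rests on the calendar alone: it equals the admission window, and patients admitted after about June cannot reach 6 months inside it. The percentages are illustrative, since they rest on uniform accrual and, for the discharge version, on an assumed stay of 0 to 14 days. Even so, keeping the 6-month loss within the 20% allowance would need 64 of 80 patients in the first month.

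The conflicting visit origins matter in their own right, because they change when the primary outcome is taken relative to the intervention. The blood-pressure conflict is a matter to reconcile, with possible unblinding of the discharge reading only. This should be corrected, and the correction is simple.

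**What to change.** 1. State June to December 2025 as the enrolment window. Give a separate last-visit date and study-end date: about mid-2026 if 6 months runs from entry, later by the length of stay if it runs from discharge.
2. Define one time origin for the 3- and 6-month visits, the same in both arms. Baseline (as in Tables 1 and 2) and discharge (already used for the remote phase in section 2.5 and for readmission in section 5.9) are both workable. Remove or clarify the post-intervention wording in section 2.1, and reconcile the intervention start and duration in sections 2.3 and 2.5.
3. Either add the 1-month assessment to section 3 and both tables or remove it from the abstract.
4. Align section 5.8 with Table 2 and section 2.2, so that outcome blood pressure is taken at baseline and at the 3- and 6-month outpatient reviews by blinded assessors. If admission and discharge readings are kept as routine care, say that they are not follow-up outcome data.

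The cost is an amendment of dates and wording. It adds no visits beyond those already scheduled, unless the 1-month assessment is kept, and follow-up into 2026 is already implied by 6-month visits for patients admitted up to December 2025.
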